**Fixed and Random effects models**

With multiple measurements from the same practice and pair, regression analysis will be used to investigate the relationship between the response variable and one or more predictors. Fixed effects regression models assume the only source of variability is between subjects (and that this was constant across all practices); adjustment will be made only for the pairing of practices. However, the data is not independent (patients within practices and pairs are more likely to be similar to one another than patients from different practices and pairs). Random effects regression models treat practice pairs as random effects, taking into account two forms of variability: within practice/pair and between practice/pair variability.

Either fixed or random effects models can be used; fixed effects will be reported.

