**2. Methodological considerations arising from previous, related work**

**2.1 Clustering**

In primary care based randomised controlled trials in the UK, designed to study the effect of educational outreach, patient level randomisation is neither practical nor ethical. Randomisation by group (practice) is preferable because it avoids contamination of the usual care group and the effect of the intervention can be assessed in the natural practice environment. Using individual patient randomisation in an educational outreach intervention directed at general practitioners is not appropriate because the management of one patient is not independent of another (MacLennan 2003).

Some studies involve randomisation of health professionals or groups of professionals (cluster randomisation) but analyse outcomes at the patient level, thus resulting in a possible overestimation of the significance of the observed effects (unit of analysis error) (Whiting -O’Keefe 1984; Donner 1981; Donner 2000; Simpson 1995; Divine 1992; Donner 1990), without making corrections for the impact of clustering. Pill tested the impact of a patient centred intervention on GPs (Pill 1998). Twenty nine general practices were randomised and the results analysed at practice level; prescribing and other changes were measured at the level of the patient. However; analysis did not take account of clustering so the results are likely to be an overestimate of the significance of the effect.

Therefore it is important to build this learning into the methodology of a trial of a new intervention in primary care general practices, directed at GPs.

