**3.5 Statistical analysis**

Pilot work found 50% of patients to have cholesterol controlled with an intraclass correlation (ICC) of 0.4. Assuming that data for 40 patients per practice would be collected, we estimated that approximately 20 practices (10 per group) would be required to detect an increase in cholesterol control to 90% in intervention practices. We anticipated a high practice dropout rate due to the length and intensity of the intervention. We, therefore, invited 49 practices to participate.

Analysis will be by intention to treat. Descriptive statistics for continuous variables will be presented as mean and standard deviation and for categorical variables, as frequencies and percentages. Baseline analysis will compare participating with non-participating practices, SOS with UC practices, and single handed with group practices. Patient level data will not be collected for non-participating practices. Summaries will use continuous and categorical variables, as appropriate. Practice-level data (e.g. number of GPs, list size) will be compared using the Wilcoxon-Mann-Whitney test, or, for comparisons between SOS and UC practices, using the Wilcoxon Signed Rank test within pairs of practices.

Due to the non-normal distribution of cholesterol levels, a log-transformation will be applied. Patient level data will be analysed at the individual level for greater power.

Linear and logistic regression models will be used to test for differences in the primary and secondary outcomes between the two intervention groups. These models will be adjusted for practice pair to account for the matching at randomisation. Results will be presented as intervention effect or odds ratio, 95% confidence interval and p-value. Secondary analyses will be carried out to investigate the sensitivity of the results to adjustments for age and sex. A sensitivity analysis, adjusting for any statin prescribing at follow up, will be carried out for the primary outcome to assess whether the treatment effect can be explained by increased statin prescribing.

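### The model to be reported adjusts for practice pair but not for practice, the randomised unit, so its standard errors are too small and its tests reject a true null too often

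*Protocol*

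**What the plan says.** Section 3.9 of the protocol matches practices in pairs on practice type (single handed or group) and on the baseline proportion of eligible patients with controlled cholesterol. It then allocates one practice of each pair to the intervention.

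Section 3.4 explains that clustering lowers power and gives the design effect. Section 3.5 supplies the inputs: "Pilot work found 50% of patients to have cholesterol controlled with an intraclass correlation (ICC) of 0.4". Section 3.5 also says of the analysis: "Patient level data will be analysed at the individual level for greater power". Linear and logistic regression models are to be adjusted for practice pair.

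The part on fixed and random effects models describes the fixed effects option as one in which variability lies only between subjects and "adjustment will be made only for the pairing of practices". It then acknowledges that patients in the same practice or pair resemble one another, so the data are not independent. The alternative is described thus: "Random effects regression models treat practice pairs as random effects". The choice is: "Either fixed or random effects models can be used; fixed effects will be reported".

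Section 2.1 faults earlier trials that randomise clusters but "analyse outcomes at the patient level, thus resulting in a possible overestimation of the significance of the observed effects" when no correction for clustering is made. Section 1.8 lists an analysis that allows for clustering among the features a new trial should have.

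**The concern.** The treatment contrast is a comparison of two practices within each pair. Its error must therefore include practice-to-practice variation within pairs. A pair effect cannot supply this, because it absorbs only what both practices have in common. Whatever else differs between the two practices coincides with the allocation and goes straight into the estimated effect. The model's standard error reflects patient-level variation and shrinks as more patients are collected per practice, although the number of randomised units stays the same.

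The protocol names the violated assumption and still selects that model. It also sizes the trial on a large ICC and then drops the ICC from the analysis. At stake are the p-values and confidence intervals for the primary endpoint and, in direction, for all the secondary endpoints. Chance differences between practices could be reported as an effect of the intervention, in either direction.

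**Working it through.** **Inputs.** Control proportion 0.50, ICC 0.4, 40 patients per practice, target 0.90 and about 10 practices per group (section 3.5); D = 1 + ρ(m − 1) (section 3.4); one practice per pair randomised (section 3.9). Alpha and power are not stated with the calculation, so two-sided 5% and 80 to 90% power are assumed.

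**1. The plan's own sample size.**
- D = 1 + 0.4 × 39 = 16.6.
- Patients per arm without clustering: n = [1.96·√(2·0.7·0.3) + z·√(0.5·0.5 + 0.9·0.1)]² / 0.4². This gives 20 at 80% power and 26 at 90%.
- Practices per arm: 20 × 16.6 / 40 = 8.3, and 26 × 16.6 / 40 = 10.8. With a continuity correction at 80% power, 25 × 16.6 / 40 = 10.4.
- At 10 practices per arm, the effective size is 400 / 16.6 = 24.1 patients and power is about 88%.

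So about 10 per group is reproduced, but only with the design effect. Without it, 20 to 26 patients per arm would be less than one practice.

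**2. Type I error of the pair-adjusted model.** Let ρ be the between-practice correlation left within pairs. The true variance exceeds the model variance by roughly 1 + 39ρ, so the two-sided error is about 2[1 − Φ(1.96/√(1 + 39ρ))]. The last column gives the range over separate null simulations with 10 pairs and 40 patients per practice. They used pair-stratified tests and differed partly in the scale on which the ICC was defined.

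| Residual ρ | 1 + 39ρ | SE too small by | Type I error, formula | Type I error, simulated |
|---|---|---|---|---|
| 0.40 | 16.6 | 4.07 | 63% | 61–68% |
| 0.20 | 8.8 | 2.97 | 51% | 46–60% |
| 0.10 | 4.9 | 2.21 | 38% | 31–48% |
| 0.05 | 2.95 | 1.72 | 25% | 21–36% |
| 0.02 | 1.78 | 1.33 | 14% | 11–21% |
| 0.01 | 1.39 | 1.18 | 10% | 8–10% |

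**3. The planned logistic model itself.** Logistic regression with pair indicators and arm was fitted under the null (1000 runs per setting, 10 pairs, 40 patients per practice).
- Total ICC 0.4, pairing removing none, half or 80% of the practice variance: error 64.5%, 58.1% and 44.6%.
- Total ICC 0.05, same three cases: 27.2%, 16.1% and 9.7%.
- 15 pairs, total ICC 0.4, half removed: 59.3%, so more practices do not cure it.
- A paired t-test on practice proportions, in the same data sets: 3.8% to 5.8%.

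**4. The random effects alternative.** Take a linear outcome with unit variance, 10 pairs, 40 patients per practice and total ICC 0.4, half of it shared by the pair. Fixed-pair and random-pair models gave the same standard error, 0.059. The true variance of the effect is 2(0.2 + 0.6/40)/10 = 0.043, a standard deviation of 0.21 (0.22 in simulation). A random effect for pair alone therefore does not repair the fault.

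**5. Larger clusters.** Section 3.8 collects all eligible patients except in the five largest practices, but gives no counts. If there were 100 to 200 per practice (an assumption), a residual ICC of 0.05 would give variance ratios of 1 + 99 × 0.05 = 5.95 and 1 + 199 × 0.05 = 10.95, and error rates of 42% and 55% by the formula in step 2.

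**The case against.** The best counter-argument is that 0.4 is a pilot ICC before matching, for one outcome. Pairs are formed on the baseline value of the primary outcome, so the correlation left within pairs may be much smaller. That stands, and it makes the 4-fold and 63% figures an upper end. It does not change the direction: the error rate exceeds 5% at every residual value examined.

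Other points limit the wording but not the defect:
- The rates are two-sided. About half of the false rejections would favour usual care, so false claims of benefit run at roughly half the listed rates, against a nominal 2.5%.
- No ICC is given for the secondary endpoints, so the size of the problem there is unknown. For subgroup interactions on characteristics that vary within a practice, such as age or sex, the practice effect largely cancels.
- The random effects description also mentions variability within and between practices or pairs, which could be read as including a practice term. None is specified, and that model is not the one to be reported.
- Analysing individual records is not itself wrong. A patient-level model with a practice term is valid and can gain some efficiency from covariates and unequal cluster sizes.
- The plan makes a partial correction through pair, whereas section 2.1 criticises trials that made none.

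The absence of a statistical analysis plan is no defence, because the protocol itself fixes the reported model.

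**Conclusion.** The concern holds and must be fixed. The reported model omits the randomised unit, so its standard errors are too small and its tests anti-conservative. The size depends on the residual within-pair ICC, which the protocol does not give. At 40 patients per practice, the formula puts the type I error between about 10% (residual ICC 0.01) and about 63% (0.40, pairing removing nothing), with intervals too narrow by a factor of about 1.2 to 4.1. Larger practices would make it worse at a given ICC. The simulations assume equal cluster sizes and normally distributed practice effects on the logit scale; the direction of the error follows from the design and does not depend on these.

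**What to change.** Replace the reported model. Either of these respects the design:
- a logistic (or linear) mixed model with pair as a fixed effect and a random intercept for practice, using small-sample degrees of freedom (the number of pairs minus 1 is a natural choice);
- a paired t-test on within-pair differences of practice-level results.

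A variance estimate clustered on practice with a small-sample correction, keeping pair, is a possible alternative. Name one as primary and apply it to the primary endpoint, all secondary endpoints, the adjusted and sensitivity analyses and the subgroups. Remove the sentence choosing fixed effects for reporting. Remove the greater-power rationale, or restate it so that it does not imply that the practice can be ignored. State explicitly that any random effect is on practice.

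The cost is analysis wording only; no new data are needed. Intervals will be wider, and the analysis will then match the clustering assumption on which the 20 practices were calculated.

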**3.6 Ethical approval and study registration**

Ethical approval was granted in December 2002 (Appendix II). At that time the intervention was called ‘clinical facilitation’. A cost effectiveness analysis is planned to report after 10 years of follow up. As the unit of intervention, all practices provided written consent to participate. The study is registered: ISRCTN61233866.

**3.7 Funding**

NHS Greater Glasgow and Clyde. The study design, funding and governance are independent from commercial sponsorship of any kind.

**3.8 Participating practices and patients**

Practices will be asked to identify patients who had confirmed vascular disease. These patients are at ≥ 30% risk of suffering a cardiovascular, cerebrovascular or peripheral vascular event in the next 10 years. In accordance with GG&C Cholesterol Guidelines (Appendix III), this level of risk will be confirmed by the following confirmed diagnoses:

- Myocardial infarction;
- CABG / angioplasty;
- Angina/IHD;
- Angiographic coronary artery disease;
- Stroke/transient ischaemic attack;
- Peripheral ischaemic arterial disease/intermittent claudication;
- Diabetic patients aged over 45years.

A validated computer search of each general practice’s computerised patient record will generate a list of eligible patients. Each patient’s computerized and paper record will then be screened to collect relevant data.

Due to time and resource limitations, a systematic sample of every third eligible patient’s data will be collected in 5 practices with the largest list sizes (12330, 7354, 7215, 7099 and 5616 patients). Therefore, cross sections of data will be collected at baseline. In addition, in all practices, some demographic data (in particular, the “Patient identification number”) may not be available. Both factors preclude longitudinal follow up of all patients. In all practices, data will be collected from each eligible patient’s record, anonymised in the practice and entered onto an ACCESS database.

**3.9 Randomisation**

**Sequence generation**

Due to the relatively small number of recruited practices and practice level randomisation, only two strata will be used (Pocock 1983). To maximise the chances of practices in the intervention and UC arms of the study being comparable at baseline, we will separate practices into prognostic factors thought to impact on the primary endpoint: Single Handed (SH) or Group (G, more than one full time GP) and the proportion of eligible patients whose cholesterol is controlled at baseline. This distinction will be made because we suspect that larger practices are more likely than single handed practices to implement the SOS intervention. Though we are not aware of an evidence base surrounding this, we suspected that Group practices would have three features favouring better uptake of the SOS intervention:

1. Multiple partner practices would have more advanced record keeping, systematic case finding, call /recall systems;

2. Greater capacity and flexibility to absorb additional work incurred by the intervention;

3. More spare rooms, enabling a pharmacist to work with the practice team on the same day each week. This would tend to increase the chances of the intervention working.

To minimise imbalance between SOS and UC practices in proportions of patients with cholesterol controlled, our framework had this as a secondary division. We used the ratio:

| | Number of eligible patients with cholesterol in target range | | --- | | Number of eligible patients | |
| --- | --- | --- |

Within their strata (SH or G), practices will be arranged in ascending order according to this ratio, ordered then numbered sequentially, and paired (practice 1, practice 2), (practice 3, practice 4) etc.

This approach to randomisation will minimize the differences from these prognostic factors, between treatment groups, to validate the assumption that any differences seen in the outcomes were most likely due to differences between the SOS intervention and UC and not random imbalances in baseline characteristics between practices in the SOS and UC arms.

**Allocation concealment**

A table of random numbers (MINITAB statistical software) will be used with one practice from each pair randomly allocated the number “1” and the other allocated “0”. Practices will not be identifiable by name: the practice’s unique Community Health Index number will be used as the only identifier, until after randomization is complete. This process ensures a balanced allocation of practices between SOS and UC arms in respect of Practice status (SH or G). This type of matched cluster design (‘matched pair’ in which one of two matched clusters in a stratum are randomly assigned to each intervention) is frequently adopted in cluster randomised trials (Donner 2000).The allocation was therefore based on clusters rather than on individuals, and the identity of all the practices will be concealed until after allocation to SOS intervention or UC.

**Implementation**

The allocation sequence will be generated by [name] ([name]). [name] (RL) will assign practices to the SOS intervention or UC.

**Blinding**

In common with trials of other educational interventions, double blinding was not possible. The study will be assessor blind, because baseline data will be collected before allocation. At follow up, two independent researchers will collect prescribing and cholesterol outcome data. Both will be blinded to whether practices had received the SOS intervention or UC, therefore bias in the process of data collection will be minimised.

**4. The Statin Outreach Support intervention**

Appendix IV summarises the process of the SOS intervention. This summary will be used as an aide memoire by practice staff. Pharmacists delivering the SOS intervention will introduce, discuss and reinforce the main messages from the cholesterol guideline during three face to face meetings between December 2003 and December 2004. Between meetings, the pharmacist will work in the practice one day per week, to understand and whenever possible, improve the practice’s attempts at introducing a systematic approach to offering simvastatin 40mg to eligible patients. The gap between meetings will be approximately 4 months, depending on the availability of the GPs, size of the practice and pharmacists’ annual leave.

**4.1.1 Overview**

Pharmacists will identify the names and contact details of eligible patients (who are not prescribed simvastatin 40mg). The pharmacist will then help the practice to agree on whether, how and when to introduce a new prescription for simvastatin 40mg for eligible patients with established vascular disease, on a case by case basis. Pharmacists will encourage GPs to adopt and apply the same approach to statin use (i.e. guideline based) for incident patients as they encountered them during routine practice.

**4.1.2 Before the first meeting**

Pharmacists will be asked to work in their allocated practice one day each week for approximately one year. They plan to access, collect and summarise patient level information to confirm that each patient who is eligible for a statin is offered one, or is currently prescribed a statin, and if not, reasons recorded. This involves confirmation of eligible diagnoses, statin prescribing (current and historical), prescription ordering, cholesterol tests and levels. Practice disease registers will be validated and updated or amended where necessary. Confirmation of diagnoses will be sought by looking through case notes, computer records or hospital (including Accident and Emergency) discharge letters.

Reasons for patients not receiving a statin will be collected. From pilot work, these are likely to be due to failure of the practice to offer the patient a statin; the patient defaulting routine appointments; dropout from prescription ordering; a history of statin intolerance or contraindication. Some eligible patients may be overlooked by their practice. In this case, the pharmacist will be asked to reinstate the patient onto the relevant disease register, in order that they would be subject to routine call and recall for review by the practice, or contacted with the offer of statin initiation. In pilot work, pharmacists noticed that patients had moved house but the new address had not been entered onto the practice computer system, meaning the patient would not have received notification of the need for an appointment at the practice if a letter had been sent.

Pharmacists will be asked to use the time in the practice to collect and summarise eligible patient level information on diagnoses, statin prescribing history and cholesterol levels. Baseline information (collected prior to randomization) will be used as a starting point for this process. Pharmacists will be asked to identify prescribing traits and gaps in care e.g. lack of cholesterol levels which limited the practices’ ability to better manage eligible patients. The prescribing traits of individual GPs will be recorded whenever possible, to provide a rich source of information to individualise attempts to improve prescribing.

Pharmacists’ perceptions of organisational barriers to increasing the uptake of simvastatin prescribing will be recorded. The pharmacist will form a plan to support the practice in finding ways to engage and implement the key messages of the educational sessions.

**4.1.3 Meeting one**

Each pharmacist will receive clear instruction to address the following three objectives during meeting one:

- enable relationship building between pharmacist and practice staff;
- evaluate the GP or nurse’s awareness and understanding of the HPS trial and statin prescribing guidelines;
- identify perceived barriers to changing statin prescribing in line with guidance.

This face to face interactive discussion will include a power point presentation, involving the pharmacist and each GP, nurse and other practice staff.

The first meeting will help the GP or nurse understand the SOS intervention process. An open, honest exchange will be encouraged. The pharmacist will use open questions to explore the GP or nurse’s usual statin prescribing practice. For example, asking which statin was prescribed first line, at what point statins were initiated (what was the trigger for initiating a statin), whether patients were assessed for a statin (and other secondary preventive medicines) opportunistically or through planned appointments, was an up to date cholesterol and whether the GP believed that liver function test results needed to be present before statin prescribing. The pharmacist will ask about the GP or nurse’s awareness and views on the recent Heart Protection Study and local guideline.

A summary of the practice’s statin prescribing (numbers of patients, statin type, dose, trends over the past few years, cost), will be shared and discussed during the meeting. Other practices’ prescribing will be used as a comparison. Pharmacists will ask GPs and nurses if they wish to hear the views of ‘educationally influential’ local opinion leaders and if so, who these opinion leaders are. The pharmacist will offer to contact these opinion leaders, with a view to feeding back answers to the GP/nurse during the second meeting. The group of pharmacists will be encouraged to contact each other and if similar questions arose from GPs or nurses in other practices, share learning across the network.

The pharmacist will be asked to establish, from each GP and nurse, what they considered to be their own and their practice’s key barriers to systematic offering of simvastatin 40mg to each (eligible) patient not prescribed it. If this discussion progresses well, targets will be agreed, for the desired proportion of patients with statins and cholesterol controlled, in their practice, at the end of the intervention. Benefits to some GPs may be conceptualised in terms of achievement of contract points and therefore remuneration for the practice, or the prospect of systematically offering evidence based prescribing for patients at highest risk. Cost savings will be projected, in view of the lower cost of simvastatin compared with other statins (one month’s supply of the preferred SOS statin (generic simvastatin 40mg) was £1.32; a commonly prescribed equivalent was Atorvastatin 20mg once daily, costing £26.64 per month).

